### Inclusion criteria

Patients ≥18 years old with histologically confirmed malignancy.Patients with radiosensitive malignancy (e.g. breast, prostate …) and oligometastases (i.e. ≤ 3 metastases) OR patients with radioresistant malignancy (e.g. renal cell carcinoma, melanoma, …) and an unlimited number of metastases.In an oligometastatic setting, all visible metastases should be treated with MDT. For patients with more than 3 radioresistant metastases, only the symptomatic lesion will be treated with SABR.Metastatic lesion must be visible on CT and < 5 cm in largest diameter.Patients with ECOG Performance Status ≤1.Patients who have received the information sheet and signed the informed consent form.Patients must be willing to comply with scheduled visits, treatment plan, and other study procedures.Patients with public health insurance coverage.

### Exclusion criteria

Patients with life expectancy < 6 months.Patients with previous radiotherapy to the metastatic area excluding stereotactic re-irradiation to the required dose level.Patients with significantly altered mental status or with psychological, familial, sociological or geographical condition potential hampering compliance with the study.Individual deprived of liberty or placed under guardianship.

### Interventions

A minimum of thirty patients will be included for each dose level. The different treatment regimens and their biological effective doses (BED_10Gy_) and equivalent dose in 2 Gy per fraction (EQD_2Gy_) are presented in Table 2. Calculations for BED_10Gy_ and EQD_2Gy_ are made using an alpha/beta ratio of 10 and 2, respectively. An interval of at least 24 weeks from the first patient treatment to the next patient treatment at each dose level will be respected. In the meantime, more patients will be included in the previous dose level, in an effort to establish the secondary endpoints. In case 1 to 5 patients present with DLT at 6 months after SABR, 30 additional patients will be included at the same dose level.

**Table 2 Tab2:** Fractionation schedules

Level	Fractions	Interval	Dose/fraction	Total	BED_10Gy_	EQD_2Gy_
1	5	48 h	7	35	59.5	78.75
2	3	48 h	10	30	60.0	90
3	1	NA	20	20	60.0	110

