**Methods:**

The DESTROY-trial is a non-randomized prospective phase I trial determining a regimen of choice for patients with non-spine bone and lymph node metastases. A total of 90 patients will be included in three different treatment regimens. They will be offered stereotactic ablative radiotherapy in 5, 3 or 1 fractions. Dose-limiting toxicity will be recorded as primary endpoint. Acute and late toxicity, local response and local recurrence, and progression-free survival are secondary endpoints. Liquid biopsies will be collected throughout the course of this study from the second fractionation schedule on.

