### Objectives

Primary endpointTo determine the maximum tolerated dose (MTD): the maximal tolerated dose will be defined as the dose level below which at least 10 patients present with a dose-limiting toxicity (DLT) at 6 months after SABR.DLT will be defined as any acute grade 3 or 4 toxicity. The DLT observation window is 24 weeks after SABR was delivered. The severity of toxicity will be graded using the Common Terminology Criteria for Adverse Events (CTCAE), version 4.03. For events not reported in the CTCAE version 4.03, the investigator will use the grade or adjectives reported in Table 1.Secondary endpointsTo assess acute and late toxicities following SABR: acute as well as late toxicity will be assessed using the CTCAE version 4.03.To evaluate local response (LR) and local failure (LF): LR will be evaluated by the response evaluation criteria in solid tumors version 1.1 (RECIST v1.1). LF will be scored as an event if an irradiated lesion shows an increase in size of ≥20%, according to RECIST v1.1.To evaluate progression-free survival (PFS): PFS is defined as the time from inclusion to documented disease progression according to RECIST v1.1 or any other clinically relevant definition (e.g. biochemical progression in prostate cancer) or death from any cause.

**Table 1 Tab1:** grade of toxicity

Grade	Adjective	Description
Grade 1	Mild	Does not interfere with patient’s usual function
Grade 2	Moderate	Interferes to some extent with patient’s usual function
Grade 3	Severe	Interferes significantly with patient’s usual function
Grade 4	Life-threatening	Results in a threat to life or in an incapacitating disability
Grade 5	Death	

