### Statistical analysis

#### Sample size

For each dose level, a minimum of 30 patients will be included. The maximal tolerated dose will be defined as the dose level below which at least 10 patients present with a DLT at 6 months after SABR.

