SABR is also often used for treating metastases from radioresistant tumors like renal cell carcinoma or malignant melanoma. Radioresistance may be overcome with dose escalation, particularly by increasing the dose per fraction [9]. A systematic review of Kothari ea. evaluating the use of SABR found excellent LC rates and low rates of toxicity for intracranial and extracranial metastatic renal cell carcinoma [26]. They reported a weighted one-year LC rate of 86% and grade 3–4 toxicities ranging from 0 to 4%. In the setting of oligometastasized malignant melanoma, there is less clinical data available. Nevertheless, a prospective study showed high rates of complete response and durable metastasis control with SABR for extracranial metastases of malignant melanoma, including bone and lymph node metastases [27]. Both for malignant melanoma and for renal cell carcinoma, LC rates achieved are comparable to those obtained with SABR for other histologies, suggesting a dominant mechanism of in vivo tumor ablation that overrides intrinsic differences in cellular radiosensitivity between histologic subtypes [28].

The concept of a risk-adapted approach for SABR fractionation regimens, using smaller fraction sizes for tumor locations that overlap with organs at risk for toxicity, has gained widespread acceptance. This concept is based on the assumption that fractionation relatively decreases the EQD2 for normal tissues. The results of this dose escalation trial, with increasing dose per fraction, can help to improve the risk-adapted approach for non-spine bone and lymph node metastases. Also important in this regard is the alpha/beta ratio of 10 used in the BED calculations, which is an estimate of the general alpha/beta ratio of tumor metastases. However, the available clinical data support the use of a lower alpha/beta for renal cell carcinoma, breast or prostate cancer, which would lead to a higher BED.

To keep the study protocol accessible to most metastasized patients, there is no limitation on the use of concurrent systemic treatment, but this gives a possible increase in acute or late toxicity.

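### The stated DLT rules leave 6 to 9 DLTs without an action and give no denominator, so 1 of 30 triggers an expansion while 9 of 30 triggers nothing

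*Protocol article*

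**What the plan says.** Three places in the protocol article bear on this point.

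- **Interventions.** The cohort size is a minimum: "A minimum of thirty patients will be included for each dose level". The only action tied to a DLT count is "In case 1 to 5 patients present with DLT at 6 months after SABR, 30 additional patients will be included", at that same level. The section also provides for extra patients at the previous level during the 24-week interval between levels.
- **Objectives.** The MTD is the "dose level below which at least 10 patients present with a dose-limiting toxicity (DLT) at 6 months after SABR". I read this as the level below the one at which 10 or more patients have a DLT. A DLT is any acute grade 3 or 4 toxicity, observed over 24 weeks.
- **Statistical analysis, Sample size.** The minimum of 30 is repeated, then the threshold: "The maximal tolerated dose will be defined as the dose level below which at least 10 patients present with a DLT". No target DLT rate, error rate or derivation of the numbers 30, 5 or 10 is given.

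The abstract gives the total as fixed: "A total of 90 patients will be included in three different treatment regimens".

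**The concern.** The two cut-points do not meet. A level with 1 to 5 DLTs is expanded and a level with 10 or more reaches the MTD threshold, but 6, 7, 8 and 9 belong to neither rule. Within the stated rules, a lower observed toxicity can therefore draw a prescribed response when a higher one draws none. Neither count has a denominator, so it is also unclear whether 10 means 10 of the first 30, 10 of 60 after expansion, or 10 of however many patients have been entered.

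At stake is the primary endpoint and the exposure of patients at the next level. The rule governs enrolment and escalation while the trial runs, so an analysis plan written later cannot repair it. Nor is this a detail that an article leaves to a fuller document: the article itself prints the rule, and prints the MTD threshold twice.

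**Working it through.** **Plan's own figure.** 3 levels × 30 patients = 90, which agrees with the abstract. This total contains no expansion. One, two or three expansions of 30 give 120, 150 or 180.

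**Step 1: coverage of the stated rules, taking the first 30 patients as denominator (an assumption, since the article states none).**

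| DLTs of 30 | Proportion | Stated action |
|---|---|---|
| 0 | 0% | none in words; escalation implied |
| 1 to 5 | 3.3% to 16.7% | 30 more patients at the level |
| 6 to 9 | 20.0% to 30.0% | none |
| 10 or more | 33.3% or more | MTD threshold reached |

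Exact (Clopper-Pearson) 95% intervals: 1/30 gives 0.1% to 17.2%; 9/30 gives 14.7% to 49.4%. The first result has a prescribed response and the second has none.

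**Step 2: the threshold after expansion.** If the count of 10 is cumulative, it corresponds to 10/60 = 16.7% in an expanded level, against 10/30 = 33.3% in an unexpanded one. A level at 16.7% would then reach the threshold while a level at 9/30 = 30% would not. The text does not exclude this reading.

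**Step 3: how often the gap is hit.** With X ~ Binomial(30, p), P(gap) = Σ C(30, x) pˣ (1 − p)³⁰⁻ˣ for x = 6 to 9. The rates p are assumed, because the article gives no planning rate.

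| True DLT rate p | P(0) | P(1 to 5) | P(6 to 9) | P(10 or more) |
|---|---|---|---|---|
| 4% | 29.4% | 70.5% | 0.1% | <0.1% |
| 10% | 4.2% | 88.4% | 7.3% | <0.1% |
| 15% | 0.8% | 70.3% | 28.0% | 1.0% |
| 20% | 0.1% | 42.6% | 51.1% | 6.1% |
| 25% | <0.1% | 20.2% | 60.1% | 19.7% |
| 30% | <0.1% | 7.7% | 51.2% | 41.1% |

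These are probabilities for one dose level at its first 30 patients. The gap probability peaks near p = 25%. From 20% to 30% the gap is the most likely of the four outcomes.

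**Step 4: the low end.** The only grade 3–4 rate in the article is in the Discussion, which reports "toxicities ranging from 0 to 4" per cent from a systematic review of renal cell carcinoma metastases. I use 4% as an illustration only. Allowing expansion and a cumulative count, P(threshold) = P(X ≥ 10) + Σ P(X = x) · P(Y ≥ 10 − x) for x = 1 to 5, with X and Y independent Binomial(30, 0.04). The result is about 0.008% per level. If DLTs are that rare, the definition of the MTD will almost certainly not be met at any level, and the article does not say what is then reported as the MTD.

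**The case against.** The strongest reply has four parts.

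*The article never says that a level with 9 DLTs is passed.* This is right. A reader might infer that nine in 30 lets the trial go on and that the escalation rule runs backwards. The documents do not support so much: they are silent on 6 to 9, and a definition of the MTD is not a permission to escalate. What stands is that nothing stated prevents it.

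*The denominator of 30 is assumed.* Also right: 30 is a minimum, and patients may be added at a level during the interval. If 10 is meant to apply to 60, it equals the 5/30 at the top of the expansion range (16.7% each), and the two numbers would fit together. But 6 to 9 of 30 (20% to 30%) would then lie above that proportion and still have no stated action. The uncertainty about the denominator is part of the defect.

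*At low DLT rates the gap hardly arises.* This is correct: 0.1% at a true rate of 4%. The concern has practical weight only at rates of roughly 10% and above. The article does not rule these out. It describes escalation by increasing dose per fraction, allows any concurrent systemic treatment, and itself notes that this may raise toxicity.

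*The primary endpoint is still reported if no level reaches 10.* A reader might infer that the trial would then return nothing. That goes too far: the abstract records DLT as the primary endpoint, and Data analysis records the incidence of toxicity. What is missing is narrower, namely the statement of the MTD result in that case. Nor is the 0–4% range a planning rate, since it comes from a review of one tumour type that includes intracranial lesions. It cannot show that the threshold is unreachable in this trial.

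**Conclusion.** The point holds as a defect in a stated decision rule. Four counts (6, 7, 8 and 9) have no action, neither rule has a denominator, and the judgement of an expanded cohort is undefined. This conclusion rests on the text alone and needs no assumed rate.

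Its size does depend on the unknown DLT rate: negligible at 4%, about one level in 14 at 10%, more than a quarter at 15%, and half or more from 20% to 30%. A reader might take the last figures as more than half of trials. They are per dose level, on the first 30 patients, and should not be read as a rate over a three-level trial.

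Because the rule defines the primary endpoint and controls exposure at the next level, it should be corrected even if low rates are expected. The missing statement for an MTD that is not reached is a secondary point, and the 0.008% behind it is illustrative.

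**What to change.** Reconcile the Objectives, Interventions and Sample size sections into one rule, best given as a table. Every DLT count, of 30 and of 60 after expansion, should have a stated denominator and a stated action. It should also say how the rule applies when more than 30 patients have been entered at a level. The sponsor and the investigator choose the actions, and they should check that the order of the actions is consistent with the order of the DLT proportions. This review proposes no action for any count.

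Add two sentences: that the MTD is reported as not reached if no level meets the threshold, and that the DLT proportion at each level is reported with an exact 95% confidence interval. With 0 of 30, for example, the two-sided upper limit is 11.6%, which is informative whether or not an MTD is found.

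The cost is a short amendment. It may also bring an expansion where the present text gives none, and so more patients than the 90 in the abstract. That total already leaves no room for the expansions that the plan prescribes, and it should be restated with its possible range (90 to 180 under the present expansion rule).

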### Time schedule and follow-up

The aim is to recruit the necessary number of patients within a timeframe of 48 months. Follow-up of these patients will be life-long in order to correctly estimate the secondary endpoints (Table 3). Patients are seen centrally by the clinical research physician at 3 and 6 months after SABR. At 6 months, repeated imaging is performed in the study to assess local control. All imaging is considered standard and should minimally include a CT of the irradiated lesion (s) but might also include MRI and/or PET-CT (with whatever relevant tracer) if standard for that malignancy. Reports on acute toxicity will be expected within 2 months after closure of the trial.

**Table 3 Tab3:** Time schedule

	TRIAL PERIOD						FOLLOW-UP		
	Screening visit	Pre-study	During study				Year 1	Year 2	Year 3 till ∞
			Every SABR fraction	Last day of SABR	3 months after SABR	6 months after SABR	Every 3 months	Every 6 months	yearly
Informed consent	x								
Clinical examination	x			x	x	x	x	x	x
Registration of toxicity		x		x	x	x	x	x	x
Registration of QoL		x		x	x	x	x	x	x
Blood sample		x	x	x	x	x			
Imaging						x			

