#### Data analysis

All data will be prospectively collected. Electronic case report forms will be used; database will be excel-based and Access-based. Statistics will be carried out using the latest version of SPSS. The primary endpoint MTD will be evaluated at 6 months after the end of SABR. The incidence of acute and late toxicity will be recorded. Chi-square test will be used to find out the significance of results. Disease free survival will be calculated using Kaplan Meier actuarial analysis. Survival times are defined from the date of start of the treatment until an event or last follow up.

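### Study imaging is scheduled only at 6 months but survival times run to last follow-up, so later RECIST-based estimates are too favourable to the extent that progression is missed

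*Protocol article*

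**What the plan says.** All references are to the protocol article.

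- **Time schedule and follow-up:** "At 6 months, repeated imaging is performed in the study to assess local control". In Table 3 the imaging row has a single mark, at 6 months after SABR. The columns for year 1, year 2 and year 3 onward carry clinical examination, toxicity and quality of life, but neither imaging nor a blood sample.
- **Same section:** "Follow-up of these patients will be life-long in order to correctly estimate the secondary endpoints". Imaging is described as standard, and its required minimum is a CT of the irradiated lesion or lesions.
- **Objectives, local failure:** "LF will be scored as an event if an irradiated lesion shows an increase in size of ≥20" per cent by RECIST v1.1.
- **Objectives, PFS:** "PFS is defined as the time from inclusion to documented disease progression according to RECIST v1.1 or any other clinically relevant definition", with biochemical progression in prostate cancer as the example, or death from any cause.
- **Data analysis:** "Disease free survival will be calculated using Kaplan Meier actuarial analysis" and "Survival times are defined from the date of start of the treatment until an event or last follow up". Kaplan-Meier is named for no other endpoint.

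**The concern.** A 20% increase in lesion size cannot be recorded without a scan. After 6 months the study requires none, yet the stated rule keeps a patient at risk and event-free until last contact. A patient examined once a year and never scanned adds years of progression-free time that nobody has verified.

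This affects the secondary efficacy endpoints, which the article gives as the reason for life-long follow-up. Its Discussion also names efficacy as one of the grounds for choosing a regimen. If later progressions are missed, PFS after 6 months leans upward, and so does any local-control curve built on the same rule. The rule is stated in the article, so it is not a detail simply left to a separate analysis plan.

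**Working it through.** **1. Is there a figure to reproduce?** No. The article gives no event count, rate or power for PFS or local control, so only the direction of the bias can be derived from it. Its size has to be illustrated under assumptions.

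**2. Direction.** Let S(t) be the true event-free proportion. Suppose the 6-month scan finds every progression up to 6 months, which favours the plan because that scan need only cover the irradiated lesions. Let q be the share of later progressions found through routine scans, markers or symptoms. If the rest are carried event-free to last follow-up, the curve reads

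S_read(t) = S(6) − q[S(6) − S(t)] = S(t) + (1 − q)[S(6) − S(t)].

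This exceeds S(t) for every q below 1. The article does not give q.

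**3. PFS illustration.** Inputs: about 20% disease-free at 2 years (the prostate figure in the Discussion, used as an assumption) and a constant hazard.

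- h = −ln(0.20)/24 = 0.0671 per month
- S(6) = 0.20^(6/24) = 0.669 and S(24) = 0.200, so S(6) − S(24) = 0.469

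With missed events never surfacing, the 24-month reading is 0.200 + (1 − q) × 0.469. A Kaplan-Meier simulation (90 patients, follow-up 12 to 48 months) agreed: 42.9% at q = 0.5 and 54.8% at q = 0.25.

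**4. Relaxing the harshest assumption.** Let missed events surface after an exponential delay with mean m months. The 0.469 is then replaced by the proportion that has progressed but not yet surfaced at 24 months:

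U = h[S(24) − S(6)·exp(−18/m)] / (1/m − h).

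- m = 6: U = 0.0671 × (0.200 − 0.669 × 0.0498)/(0.1667 − 0.0671) = 0.112
- m = 12: U = 0.0671 × (0.200 − 0.669 × 0.2231)/(0.0833 − 0.0671) = 0.209 (unrounded inputs)

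24-month PFS reading, true value 20%:

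| q | never surface | mean delay 12 months | mean delay 6 months |
|---|---|---|---|
| 0.80 | 29.4% | 24.2% | 22.2% |
| 0.50 | 43.4% | 30.5% | 25.6% |
| 0.25 | 55.2% | 35.7% | 28.4% |

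The first column is therefore an upper-end illustration.

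**5. Local control, if it were plotted the same way.** Take 90% at one year (the Discussion reports more than 90%) and a constant hazard: S(6) = 0.90^0.5 = 0.949 and S(24) = 0.90² = 0.810. With missed events never surfacing, the 2-year reading is 83.8%, 87.9% or 91.4% at q = 0.80, 0.50 or 0.25. The article specifies no such curve, so these figures are conditional on one being drawn.

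**6. Does censoring at the last scan cure it?** Not by itself. With no scans after 6 months, every event-free patient leaves the risk set at 6 months. With symptom-driven scans, censoring becomes informative. Suppose follow-up is 36 months (assumed), later progressors are scanned with probability p, non-progressors with probability r, and everyone else is censored at 6 months. With S(36) = 0.20^1.5 = 0.0894,

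S_read(24) = S(6) × [p(S(24) − S(36)) + r·S(36)] / [p(S(6) − S(36)) + r·S(36)].

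- p = r gives exactly 20%.
- p = 0.8, r = 0.5: 0.669 × 0.1332/0.5081 = 17.5%
- p = 0.8, r = 0.25: 0.669 × 0.1108/0.4858 = 15.3%

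The bias is downward when progressors are more likely to be scanned than non-progressors.

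**The case against.** **Routine scans will occur.** Imaging is called standard, and the Table 3 row is not a full list: it has no mark at screening, although eligibility requires a lesion visible on CT. This stands, and it means that q is probably above zero. But nothing after 6 months is required or timed, so the share detected is uncontrolled.

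**PFS has other triggers.** Death, biochemical and clinically evident progression all count, and examinations continue. This stands too. The effect on PFS is partial, and the prostate figure used in the illustration comes from the tumour where marker detection is most likely. Two things limit the point: Table 3 schedules no blood sample after 6 months, and the Background says that these patients often have few or no symptoms.

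**Local control is already tied to the 6-month scan, and Kaplan-Meier is named only for disease-free survival.** Correct. The local-control part holds only if the general sentence on survival times is applied to local failure.

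**Last follow-up is undefined in a condensed article and might mean last disease assessment.** Possible. But the ordinary reading is last contact, and the same article describes follow-up visits without imaging.

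**Stronger readings.** A reader might infer that all unscanned patients are wrongly event-free on both endpoints, or that later results are inflated by 10 to 35 percentage points. The documents support neither: PFS has triggers that need no scan, and no detection share is given. A reader might also infer that differences between the sequential, non-randomised dose levels would be artefacts of scanning frequency. Nothing in the article indicates that routine scanning differs between levels.

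**Conclusion.** The point holds in a limited form. With one scheduled scan and survival times that run to last follow-up, unassessed time counts as event-free for all local failure and for the part of PFS that only imaging reveals. Estimates after 6 months are then biased upward to the extent that later progression is missed.

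The direction follows from the text, but the size does not. For an assumed true 2-year PFS of 20%, the illustrations run from about 22% (80% detected, the rest surfacing after a mean of 6 months) to 55% (25% detected, the rest never surfacing). They rest on a constant hazard, complete detection up to 6 months and assumed detection shares. The 2-year local-control figures also assume a curve that the article does not specify.

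The primary dose-limiting-toxicity and maximum-tolerated-dose endpoint is untouched. The change is worth making because it is cheap and concerns a stated rule.

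**What to change.** - **Data analysis, censoring:** state that patients without an event are censored at the last adequate tumour assessment (a scan, or a marker test where progression is biochemical), with death remaining a PFS event.
- **Main local-control estimate:** use the proportion with local response or failure at 6 months, per dose level, when every patient is due to be scanned.
- **Data capture:** record the date and result of each routine scan at follow-up visits.
- **Beyond 6 months:** present PFS and local control as descriptive, with the number assessed in each interval, and repeat the analysis under last-follow-up censoring. Where scans are symptom-driven, the two rules tend to err in opposite directions. Counting deaths that occur after the last scan adds to the downward pull of last-assessment censoring. Neither curve should therefore be read as unbiased.

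The cost is analysis wording and case report form fields for routine scans. No imaging is added. Later estimates become less favourable and less precise, and may be too low if scanning is symptom-driven.
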